**Primary outcome**												
	HbA_1c_^a^	X^b^	N/A^c^	X	N/A	NA/	X	N/A	X	N/A	X	X
**Secondary outcomes**												
	Diabetes distress scale	N/A	N/A	X	N/A	X	N/A	X	N/A	X	N/A	X
	Measures of Medication Adherence Scale	N/A	N/A	X	N/A	X	N/A	X	N/A	X	N/A	X
	Summary of diabetes self-care activities	N/A	N/A	X	N/A	X	N/A	X	N/A	X	N/A	X
	Patient Health Questionnaire	X	N/A	X	N/A	X	N/A	X	N/A	X	N/A	X
	Positive affect subscale	N/A	N/A	X	N/A	X	N/A	X	N/A	X	N/A	X
	Daily assessments	N/A	X	X	X	X	N/A	X	N/A	X	N/A	X

^a^HbA_1C_: hemoglobin A_1c_.

^b^X: assessment administered.

^c^N/A: not applicable.

### Intervention Group

Participants assigned to the positive emotion regulation skills intervention will receive full access to the Happify Health platform. However, their version will feature a diabetes-related track focusing on building skills for greater happiness, reducing stress, and coping better with diabetes (Figure 1). Although the description of the track cues them to think about the impact of negative emotions on their diabetes and the benefits of increasing positive emotions, activities within the track are not focused specifically on diabetes. Importantly, although participants will be encouraged to use this particular track, they will not be required to start or complete the diabetes-related track and will be able to choose from all the other tracks available on Happify Health.

**Figure 1 figure1:**
[figure not shown]
Screenshot of the featured track description for Developing Affective HeaLth to Improve Adherence intervention.

The featured diabetes-related track was designed by Happify Health and the second author, who is an expert on emotion and diabetes. The track is based on activities and content from the Developing Affective Health to Improve Adherence intervention originally developed by Moskowitz et al [21]. The version included in this study has four parts.

#### Part 1

This part contains 8 different activities and exercises focusing on savoring. For example, in 1 activity, *Today’ s grateful moment*, participants are asked to spend a few moments writing about something they are grateful for. In another activity, *Let the good times roll*, participants make a plan to spend time doing simple things that promote positive affect and then write about how it went after completing the tasks they planned.

#### Part 2

This part contains 9 different activities and exercises focusing on reframing negative thoughts. For example, in *A week’s worth of thanks*, participants keep a gratitude journal about someone they are close to and spend time writing about why they are grateful for that person. In another activity, *Savor the small stuff*, participants spend a week doing something mindfully (eg, eating a meal or taking medication) and then write about how it went.

#### Part 3

This part contains 11 different activities that build on parts 1 and 2 but includes exercises promoting goal orientation and optimistic thinking. For example, in *Give Myself a Break*, where participants practice self-compassion and then spend time writing about how it went. In another activity, *Loving-Kindness Meditation*, participants verbalize good wishes when interacting with other people and then write about how it went.

#### Part 4

This part contains 11 different activities that promote resilience and helping others. For example, in *What am I proud of?*, participants spend some time thinking about something they are proud of and then write about it. In another activity, *Help Someone*, participants spend some time helping another person and then write about it.

Participants must complete one part before they can begin the following part, and they do so by earning either a silver medal (earned by completing all but 4 activities) or a gold medal (earned by completing all but 3 activities). Thus, participants will take varying lengths of time to complete a track, depending on their level of engagement with the platform. As participants will have access to the full Happify Health platform, if they complete the intervention track before the 8-week study period has elapsed or choose to change tracks before finishing, they will have access to all other available Happify Health tracks and instant-play activities (where they can choose to complete certain activities outside of dedicated tracks).

### Sham Digital Intervention

Participants assigned to the control condition (Figure 2) will have access to a version of Happify Health that includes only polls on various mental health topics. After each poll, participants in this condition are provided with social comparison data about how their responses to the poll compared with other users’ responses and information about why this topic is important (including references to relevant scientific studies). For example, after responding to a poll question that asks participants to indicate how often they have a deep or meaningful conversation with someone, participants will view psychoeducational information about the benefits of conversation, including that people who spend less time alone and more time talking to others tend to be happier [73] and that the happiest people have much less small talk, but many more meaningful conversations compared with the least happy people [74].

**Figure 2 figure2:**
[figure not shown]
Screenshot of the track description in sham digital intervention.

### Analysis Plan

We plan to analyze the changes in primary and secondary outcomes across the 2 conditions using hierarchical linear modeling (HLM). We will compute the change trajectories on each outcome over the course of the study assessments (ie, at baseline, immediately postintervention, and at 3-, 6-, and 12-month follow-ups). These trajectories will then be averaged together within each condition, so we can compare the trajectories for each outcome across the 2 conditions to determine if there was greater improvement in the positive emotion regulation skills intervention group relative to the control group.

We plan to use participants’ daily assessments in 2 ways. First, we will compute growth trajectories for each participant using their daily assessments to explore when people tend to experience improvements in diabetes-related distress, diabetes regimen adherence, and mood during the intervention. Second, as retrospective reports can sometimes lead to inflated or inaccurate information compared with daily assessments [75], we will use daily assessments to compute weekly averages for diabetes-related distress, diabetes regimen adherence, and mood during and after the intervention. These weekly averages will then be used as outcome variables in the same HLM analyses described earlier.

Previous research on the impact of health care interventions on people with poorly managed diabetes suggests that effects may be most effective among people with especially poor glycemic control or HbA_1c_ levels above 9.5% [76]. Consequently, we plan to examine the effects of baseline HbA_1c_ as a moderator of the effects of the intervention on changes in the primary and secondary outcomes. Similarly, we also plan to examine the effects of baseline depressive symptoms as a moderator of the effects of the intervention. Finally, given that the effects of Happify Health use are typically moderated by usage [57-61], we plan to examine the effects of frequency of usage as another moderator of changes in the primary and secondary outcomes.

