## Methods

### Recruitment Strategy

We plan to recruit participants by capitalizing on the existing process used to draw new users to Happify Health, including advertisements on Facebook and other social media sources. To attract individuals with type 2 diabetes specifically, targeted advertisements will also be posted on websites that connect potential participants with research studies and clinical trials (eg, Research Match) and on websites relevant to people living with type 2 diabetes.

Interested participants will be directed to a web-based survey to determine eligibility. The survey questions will include questions on age, location, previous Happify Health usage, diagnosed chronic illnesses, self-reported HbA_1c_ level, the Patient Health Questionnaire (PHQ) [62], and contact information. Users who meet initial inclusion criteria will then be contacted directly by Happify Health research staff to discuss the study in more detail. During this call, all eligibility questions will be readministered to ensure that the potential participant still meets the inclusion criteria. Those who agree to participate after this call will be sent an email to begin a week-long run-in period; during this run-in period, participants will be instructed to answer a brief web-based survey including three questions assessing daily diabetes-related distress, diabetes regimen adherence, and mood. Participants who complete this run-in period will then be sent an email instructing them to download the Happify Health app and to begin the study.

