### Procedures

Participation in this study will take place over approximately 14 months, including an 8-week intervention (or corresponding control) delivered via Happify Health as well as follow-up assessments at 3, 6, and 12 months postintervention. To ensure that HbA_1c_ levels reported postintervention reflect average glucose levels only after starting the intervention, all participants will begin the study within 3 weeks of obtaining their most recent HbA_1c_ levels. Participants who indicate that their most recent HbA_1c_ levels were obtained before that when contacted by phone will wait to begin the study until they obtain their following HbA_1c_ measurement and researchers confirm that they meet the inclusion criterion.

Once participants are ready to begin the study, they will be directed to complete 1 week of daily assessments without exposure to either condition. Participants who complete fewer than 5 of these assessments will be disqualified from the study. Those who complete at least five of the daily assessments during this qualifying period will be directed to download the mobile app and complete the regular onboarding questionnaire for Happify Health; participants will be randomly assigned to either the positive emotion regulation skills intervention group or the control group upon completing these questions. Following randomization, participants will be prompted to complete the baseline assessment.

Participants will then be instructed to begin using their assigned version of Happify Health. Although participants will not be given explicit instructions on how often they should use the platform, they will be encouraged to engage with the platform daily. Participants will receive daily push notifications on their mobile device to remind them to access the platform and answer daily questionnaires, and they will also receive weekly emails as part of the Happify Health platform to help keep them engaged with the program. In addition, to improve use rates and participant retention, research staff will call participants to inquire about problems when a participant has not engaged with the Happify Health platform at all for 1 week.

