After 8 weeks, participants will be instructed to complete the postintervention assessment; this assessment will be identical to the baseline with the exception of HbA_1c_ assessment, which will occur 3 weeks later via the Happify Health app. After completing this assessment, participants will receive an email instructing them to answer daily questions for 1 week and to remind them that we will contact them again in 3, 6, and 12 months for follow-up assessments and that they should continue to use their assigned version of Happify Health as they see fit. Participants will then receive emails instructing them to complete each of the 3-, 6-, and 12-month assessments, which will also be accompanied by 1 week of daily assessments at each follow-up period. Table 1 provides the schedule of activities. To improve participant retention, participants who do not complete the postintervention, 3-, 6-, and 12-month assessments will also receive a reminder phone call from the research staff.

**Table 1 table1:** Schedule of activities for prescreen, intervention period, and follow-up assessments.

Assessments		Time										
		Prescreen	Week 1: qualifying period	Week 2: baseline and first week of intervention	Weeks 3-9: intervention	Week 10	Week 12	Week 21: 3-month follow-up	Week 24	Week 33: 6-month follow-up	Week 36	Week 57: 12-month follow-up

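### As worded, the weekly averages of daily distress, adherence and mood begin in the first treated week, and the unexposed run-in week has no stated role as their baseline

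*Protocol article*

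**What the plan says.** All references are to the Methods of the protocol article.

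- **Run-in content.** Under Recruitment Strategy, the run-in survey has "three questions assessing daily diabetes-related distress, diabetes regimen adherence, and mood". These are the same three items used as daily assessments later.
- **Run-in timing.** Under Procedures, participants "complete 1 week of daily assessments without exposure to either condition". Anyone with fewer than 5 of the 7 reports is disqualified. The rest download the app and answer the onboarding questionnaire, and "participants will be randomly assigned to either the positive emotion regulation skills intervention group or the control group upon completing these questions".
- **Formal baseline.** "Following randomization, participants will be prompted to complete the baseline assessment". Table 1 heads this column "Week 2: baseline and first week of intervention". The daily-assessment row of Table 1 is marked for Week 1 and for Week 2.
- **First use of the daily data (Analysis Plan).** Individual growth trajectories are to explore when people improve "in diabetes-related distress, diabetes regimen adherence, and mood during the intervention".
- **Second use (Analysis Plan).** "we will use daily assessments to compute weekly averages for diabetes-related distress, diabetes regimen adherence, and mood during and after the intervention". The averages then become outcomes in the hierarchical linear model described at the start of that section. Its time points are baseline, immediately after the intervention, and 3, 6 and 12 months.

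The Analysis Plan does not mention the run-in week. The only use stated for its data elsewhere is the 5-of-7 completion criterion.

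**The concern.** The model chosen for the weekly averages needs a baseline, but the window stated for those averages contains no untreated week. If an analyst follows the wording, the first value in each daily-outcome trajectory comes from a week in which the intervention arm already has the full platform.

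Two things are at stake. First, the planned comparison is of change between arms, and any effect that appears in the first treated week becomes part of the starting level and is not counted as change. Second, the trial holds a pre-randomisation measure of each item, from at least 5 days for every eligible randomised participant, and the plan does not say that it will be used. Adjusting for it would usually sharpen the comparison. The daily items are meant to carry some weight: Table 1 groups them with the secondary outcomes, and the Analysis Plan justifies them as a safeguard against inaccurate retrospective reports.

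**Working it through.** The protocol gives no effect size, SD, correlation or power for the daily outcomes, so there is no figure to reproduce. The check has three parts.

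**1. Which days fall in the stated window?** Participant Compensation pays US $1 per daily assessment.
- Intervention: US $56 = 8 × 7 days, which is Weeks 2 to 9 in Table 1.
- After the intervention: US $28 = 4 × 7 days, which is Weeks 10, 21, 33 and 57.
- The stated total agrees: 4 × 15 + 56 + 28 + 4 × 5 = US $164.

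The window therefore holds 56 + 28 = 84 days, or 12 weekly averages, all after randomisation. The 7 run-in days lie outside it. Adding them gives 13 weekly averages, one of them before randomisation.

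**2. How much of the effect is lost if change is counted from Week 2?** Let *f* be the average share of the effect at the end of 8 weeks that is already present during the first treated week. A change contrast from that week keeps 1 − *f*. The shapes below are assumptions.
- Linear build-up over 8 weeks: *f* = 0.5/8 = 0.0625.
- Exponential build-up with half-life *h* weeks: *f* = [1 − (*h*/ln 2)(1 − 2^(−1/*h*))] / (1 − 2^(−8/*h*)).

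| Build-up | *f* | Change retained |
|---|---|---|
| Linear | 6% | 94% |
| Half-life 4 weeks | 11% | 89% |
| Half-life 2 weeks | 17% | 83% |
| Half-life 1 week | 28% | 72% |
| Half-life 0.5 week | 46% | 54% |

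These shares apply to change from Week 2 to the end of treatment. A straight-line slope fitted from Week 2 also misses the early rise when build-up is front-loaded. If build-up is exactly linear, the weekly slope within the intervention period is not biased; only the accumulated change is short.

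**3. What does this mean for power, like for like?** Further assumptions: true standardised effect *d* = 0.3, correlation ρ of 0.5 to 0.7 between the starting week and the later week, and two-sided alpha 0.05. I take 112 to 144 per arm, which is 56% and 72% of 200, the 8-week response range quoted under Participants.
- Change score: effect *d*(1 − *f*), SD √(2(1 − ρ)).
- Covariate adjustment: effect *d*(1 − ρ*f*), SD √(1 − ρ²).
- The run-in week has *f* = 0.

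Example with 112 per arm, ρ = 0.5 and a change score (SD = 1). From the run-in, 0.3 × √(112/2) − 1.96 = 0.285, so power is 61%. From Week 2 with linear build-up, 0.28125 × √(112/2) − 1.96 = 0.145, so power is 56%.

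| Starting week | Change score | Covariate |
|---|---|---|
| Run-in | 61% to 91% | 74% to 95% |
| Week 2, linear build-up | 56% to 87% | 71% to 93% |
| Week 2, half-life 1 week | 37% to 66% | 61% to 82% |

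Matched case by case, the linear loss is about 4 to 6 points for a change score and 2 to 3 points for covariate adjustment. The loss is material only if the effect builds quickly. These are two-time-point illustrations, not the power of the planned trajectory model.

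**The case against.** The strongest reply is that nothing in the article says the run-in data are dropped. Table 1 marks daily assessments in Week 1, in the same row as every later wave, and the model to be used has a baseline time point. The authors may well have meant the run-in week to fill it. This stands: exclusion is an inference from the stated window.

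Three stronger readings are tempting, and the document does not support them.
- **That Week 2 daily means are the designated baseline.** A reader might infer this from the Table 1 heading. That heading marks when the baseline questionnaires and HbA1c are collected; no text gives the Week 2 daily mean that role.
- **That the growth trajectories also exclude the run-in.** The phrase about the intervention period may describe when improvement is looked for, not which days enter the model. That analysis is also exploratory.
- **That ignoring the run-in costs a calculable multiple of the sample.** The usual factor, 1/(1 − ρ²), compares covariate adjustment with a single follow-up mean and no baseline. The plan has up to 12 weekly means per person in a hierarchical model, which already absorbs stable differences between people. The correlation is not given either. No such multiplier should be claimed.

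It may also be said that choosing a baseline covariate for non-primary items is detail that an article leaves to the full protocol or analysis plan. That would answer mere silence. Here the article itself fixes a window and a model that do not fit together.

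**Conclusion.** The point holds as a conflict of wording with a practical consequence. Followed literally, the weekly-average analyses begin in a treated week, although the trial collects an unexposed, pre-randomisation week of the same items. The resulting understatement of change is small under gradual build-up (about 6%) and larger under rapid build-up (11% to 46% for half-lives from 4 weeks down to half a week). The document gives no evidence on which applies. Some precision is also forgone, by an amount that cannot be fixed without the correlation and the final model.

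The consequence is limited. HbA1c is not affected, and between-arm comparisons of later levels of the daily items remain protected by randomisation. It is a free improvement of minor to moderate severity.

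**What to change.** Amend the second paragraph of the Analysis Plan in three respects.

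1. State that the run-in (Week 1) mean of each daily item is the baseline for the weekly-average model. Enter it either as a covariate or as time 0 with a mean constrained to be equal across arms, which is justified because it precedes randomisation. For regimen adherence, score the run-in days in the same way as the later days.
2. State that Week 2 is an on-treatment week for the daily outcomes, so that the Table 1 heading is not taken to define their baseline.
3. Include the run-in days as the pre-exposure level in the exploratory daily growth trajectories, so that improvement in the first treated week can be seen.

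The cost is a few sentences of analysis text. No new data, visits or participant burden are needed. The change should be made before any outcome data are examined by arm, including the planned look when 20% of the target sample has completed the intervention.

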Observational studies of Happify Health users demonstrate that usage over 8 weeks is associated with more than a 27% increase in positive emotions, and high-use participants see even greater improvement [57,58]. A later RCT also demonstrated that Happify Health users who completed at least two activities per week reported significantly more improvement in depression, anxiety, and resilience than those who completed fewer activities or participants assigned to the control group [59]. Similar effects were obtained from RCTs focused specifically on people with higher levels of emotional or workplace distress [60]. More recent research also suggests that Happify Health use improves subjective well-being among people living with chronic physical conditions, including, but not limited to, diabetes, at the same rate as those without chronic conditions [61]. Consequently, there is preliminary evidence to suggest that Happify Health could effectively improve subjective and psychological well-being among individuals diagnosed with type 2 diabetes. However, no research has examined whether Happify Health use could also positively improve outcomes associated with their diabetes, including how well they manage their condition, their level of diabetes-related distress, and physical outcomes such as HbA_1c_ levels.

Therefore, in this study, our goal is to examine whether Happify Health use over the course of 8 weeks also helps to improve diabetes-specific outcomes. To do so, we plan to compare changes in HbA_1c_ levels among adults with poorly managed type 2 diabetes and elevated depressive symptoms who have completed 8 weeks of activities on Happify Health or 8 weeks of a sham digital intervention. Secondary outcomes include depression, positive affect, and other diabetes-specific outcomes such as medication adherence, diabetes-related distress, and diabetes-related self-care activities. In addition, although many other studies (particularly mindfulness and PP interventions) did not examine long-term effects, we plan to explore the long-term effects of Happify Health use on both primary and secondary outcomes at 3, 6, and 12 months postintervention.

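### Frequency of usage is planned as a moderator, but it arises after randomisation, is self-chosen and refers to a different product in each arm, so it can show a usage-related effect when the intervention does nothing

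*Protocol article*

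**What the plan says.** The Analysis Plan names three moderators. The first two, HbA1c and depressive symptoms at baseline, are measured before the intervention and are described as modifying the intervention's effect. For the second of these the wording is "we also plan to examine the effects of baseline depressive symptoms as a moderator of the effects of the intervention". The third is usage: "we plan to examine the effects of frequency of usage as another moderator of changes in the primary and secondary outcomes". The reason offered is "given that the effects of Happify Health use are typically moderated by usage".

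Three other places bear on what usage is:

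- **Timing.** Under Procedures, participants are randomised on completing the onboarding questions and complete the baseline assessment. Only after that comes "Participants will then be instructed to begin using their assigned version of Happify Health".
- **Amount.** The same section states that "participants will not be given explicit instructions on how often they should use the platform", although daily engagement is encouraged. After week 8, use continues at the participant's discretion.
- **Product.** The intervention arm has the full platform (Intervention Group). Control participants "will have access to a version of Happify Health that includes only polls on various mental health topics" (Sham Digital Intervention).

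Objectives of This Study describes an earlier trial in which platform users who "completed at least two activities per week reported significantly more improvement in depression, anxiety, and resilience" than lower users or controls.

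**The concern.** A moderator analysis in a randomised trial is interpretable because the moderator is fixed before assignment: within each of its levels, the arms remain comparable. Usage does not meet that condition. It can be affected by assignment, participants choose it, and the article defines no usage measure common to both arms. A frequent user of activities and a frequent answerer of polls need not be the same kind of person.

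People who are more motivated or conscientious plausibly use an app more and also look after their diabetes better. Strengths and Limitations recognises such traits, but only as a limit on generalisability arising from the run-in. The risk is that a null result by assigned arm is reported beside a positive usage result that reads as dose-response evidence. The earlier trial described under Objectives of This Study made a comparison of this self-selected kind.

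**Working it through.** **Inputs from the article.** 400 participants, 200 per arm (Participants). Response at 8 weeks in earlier trials was 56% to 72%, so the low end gives 0.56 × 200 = 112 per arm, 224 in all. The article gives no figure for the usage analysis, so there is none to reproduce.

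**Assumed inputs.** The arm effect and the usage effect are both zero. An unmeasured trait has correlation ρ with outcome improvement, r1 with usage in the intervention arm and r0 with usage in the control arm. The article states none of these, so a range is shown. Outcome and usage are in SD units, the test is two-sided at 5%, and ordinary regression on the change score stands in for the hierarchical model.

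**Arm-by-usage term.** The spurious slope difference is ρ × (r1 − r0). Its standard error is about 2/√N, which is 2/√400 = 0.100 or 2/√224 = 0.134. With z = slope/SE, the rejection rate is Φ(z − 1.96) + Φ(−z − 1.96).

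| ρ | r1 / r0 | Spurious slope | Rejection, N = 400 | Rejection, N = 224 |
|---|---|---|---|---|
| any | 0.6 / 0.6 | 0 | 5% | 5% |
| 0.2 | 0.3 / 0.1 | 0.04 | 7% | 6% |
| 0.3 | 0.6 / 0.5 | 0.03 | 6% | 6% |
| 0.5 | 0.6 / 0.4 | 0.10 | 17% | 12% |
| 0.3 | 0.6 / 0.3 | 0.09 | 15% | 10% |
| 0.5 | 0.6 / 0.1 | 0.25 | 71% | 47% |

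Simulation with 4,000 null trials per setting agrees: the last two rows give 15% and 72% at N = 400, and 10% and 48% at N = 224. Going further, to ρ = 0.5 with poll use unrelated to the trait (r1 = 0.6, r0 = 0), simulation gives 86% at N = 400.

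Equal correlations protect the test only if the usage scale is also shared. With ρ = 0.3, r = 0.5 in both arms and control usage three times as spread out, the interaction rejects in 27% of null trials at 200 per arm.

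**Other readings of the sentence.** Take the case kindest to the plan: ρ = 0.3, r = 0.5 in both arms, same scale, 200 per arm.

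- Pooled usage slope: bias 0.3 × 0.5 = 0.15, SE about 1/√400 = 0.05, z = 3.0, rejection 85% (simulation 85%).
- Intervention users above the median against all controls: a standard normal variable averages 0.798 above its median, so the bias is 0.15 × 0.798 = 0.12. SE is √(1/100 + 1/200) = 0.122, z = 0.98, rejection 16% (simulation 18%).
- Arm-by-usage term: simulation 5%.
- Comparison by assigned arm: simulation 5%, and between 4% and 6% in every setting tried.

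When the trait does not affect the outcome (ρ = 0), every test stays near 5%.

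**A threshold-based effect in users.** Suppose use of at least two activities per week were taken as compliance, with assignment as the instrument. Let p be the share of the intervention arm at or above the threshold. The estimate is the all-randomised effect divided by p, which equals (mean effect above) + ((1 − p)/p) × (mean effect below). The second term is zero only if sub-threshold use does nothing. As an illustration, assume benefit of 0.1 SD per weekly activity up to four, and lognormal use with log-SD 0.9:

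| Median use per week | p | Mean effect above | Mean effect below | Estimate | Excess |
|---|---|---|---|---|---|
| 1 | 0.22 | 0.31 | 0.09 | 0.61 | 98% |
| 2 | 0.50 | 0.33 | 0.11 | 0.45 | 33% |
| 3 | 0.67 | 0.35 | 0.12 | 0.41 | 17% |

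The excess is computed before rounding. A cut-off at two activities therefore swaps one bias for another.

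**The case against.** The Analysis Plan says only that usage will be examined. Efficacy is to be judged by comparing trajectories between conditions, and that comparison is untouched. The wording also differs between moderators: the baseline ones modify the intervention's effects, while usage modifies changes in outcomes, so an arm-by-usage term is one reading rather than a stated test. Poll use is self-paced too, under the same prompts and reminder calls. A similar relation to prognosis in both arms is therefore plausible, and the interaction would then keep its level. The definition and labelling of usage may be in a statistical analysis plan that is not shown.

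Much of this stands. It rules out three stronger conclusions that a reader might infer:

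- **That the trial's main result is compromised.** It is not: the comparison by assigned arm keeps its error rate throughout.
- **That a particular inflated error rate applies to this trial.** None can be stated, because the correlations are assumptions and the test is not specified.
- **That the investigators will credit a usage association to the intervention.** The article makes no such claim.

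The objection does not remove the point. The article places a post-randomisation variable in the same list as two baseline ones without a caveat, and a fuller definition of usage elsewhere would not make it a baseline variable. The unclear wording does not help either, since the pooled-slope and high-user readings are inflated even where the interaction is not.

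**Conclusion.** The concern holds as a point about one additional analysis. Usage as planned is a non-randomised, self-selected variable that differs in kind between arms, and it should not stand as a moderator beside baseline HbA1c and baseline depression. With no true effect and 400 participants, the arm-by-usage term rejects from about 5% (same usage-prognosis relation and same scale in both arms) to about 72% (strong, unequal relations), and beyond that only at the more extreme setting shown. In an equal case with moderate correlations, a pooled usage slope rejects about 85% and a comparison of high users with controls about 18%. These figures rest on assumed correlations and a simplified model. The direction of the argument rests only on the article's own account of when usage occurs, who chooses it and what each arm is given. The correction is worth making, but it does not put the main comparison in doubt.

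**What to change.** Take usage out of the moderator list. State that all claims of effect rest on the comparison of all randomised participants by assigned arm. Report usage-outcome associations within each arm, labelled descriptive and non-randomised.

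If an effect in users is wanted, add a complier-average estimate as a sensitivity analysis. Use assignment as the instrument and define exposure as any activity use. The sham version offers only polls, so noncompliance is one-sided within the assigned products. State the exclusion assumption: assignment has no effect on outcomes in those who would use no activity. Do not make two activities per week the sole definition of exposure. Because use may continue after week 8 while HbA1c is collected to week 57, state the period over which exposure is counted.

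The cost is a few sentences and, if chosen, one extra analysis, which brings a wider interval and an assumption that cannot be tested.
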